**Relevant concomitant care permitted or prohibited during the study**

During the follow-up period patient participants are not precluded from receiving other non-surgical treatments for their knee pain (e.g pain medication, additional physiotherapy). Utilisation of these co-interventions will be captured by the health utilisation questionnaire at 12 weeks and 6 months. Accessing knee surgery (i.e. arthroscopy) during the follow-up period would result in the patient being excluded from the study.

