^, (ii) moderate or advanced knee OA on x-ray (or Kellgren-Lawrence x-ray score ≥ Grade 3), (iii) recent trauma likely to be associated with considerable tissue damage, (iv) having an acutely swollen or locked knee, or suspicion of ligament injury on physical exam, (v) inflammatory arthritis, (vi) surgery or significant trauma of the index knee within the previous 2 years, (vii) pregnancy, (viii) unable to communicate in English (ix) preference for accessing physiotherapy treatment privately prior to the ‘best practice’ session or do not want to avail of the ‘best practice’ physiotherapy session.

There is a clear association between knee OA and DMTs, and meniscal pathology usually exists in the context of other OA changes
^
5,
59,
62
^. The EULAR clinical classification criteria will be used by GPs to rule out later stage or more advanced OA during their clinical assessment
^
49
^. These criteria state that patients aged 40 years or older with movement-related joint pain, knee morning stiffness < 30 minutes, and functional limitations have knee OA, if they also have, on examination, one or more of the following: crepitus, restricted range of motion, and bony enlargement. Should there be uncertainty on clinical exam, a GP-ordered knee x-ray will be necessary for inclusion, to exclude those with moderate or severe osteoarthritis (Kellgren-Lawrence score ≥ Grade 3). Assessment procedures will be a specific component of the training workshop for participating GPs. Patients will have their diagnosis of a DMT or early OA confirmed by the participating physiotherapists, who have expertise in musculoskeletal assessment. They will use a checklist to check and rule out any features of moderate or advanced OA. This research will promote appropriate use of advanced imaging; therefore an MRI will not be required to confirm the diagnosis of a DMT or early OA
^
27
^.

**
*Sample size and recruitment targets.*
** As this is a feasibility study and the primary aim is not to evaluate clinical effectiveness, a formal sample size calculation has not been carried out
^
54,
63
^. The purpose of the study is to investigate the feasibility and acceptability of the intervention and examine study procedures around recruitment and retention with a view to refining these, if necessary, for a future definitive trial. The feasibility of the intervention will be explored by recruiting 36 eligible patients, 15 GPs and five physiotherapists.

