### Intervention for health care professional and patient participants

The KNEE-DEeP intervention (
Figure 2) is a complex intervention designed to improve the uptake of evidence-based care for early OA and DMTs, by targeting the behaviours of both HCPs and their patients
^
48
^. Evidence based care is informed by clinical practice guidelines and focuses on patient education, exercise and promoting self-management
^
11,
15,
26
^. The KNEE-DEeP intervention will aim to ensure patients receive evidence based management and consistent information at an early point in their care from both the GP and physiotherapist, thereby reducing unnecessary referral to secondary care and inappropriate imaging. GPs and physiotherapists will receive specific training to deliver the patient intervention and enhance their skills and confidence in managing patients with this type of knee pain. Content and design of the HCPs training session will draw on evidence from a range of chronic musculoskeletal conditions
^
64–
69
^. The content of the intervention aligning to the Template for Intervention Description and Replication (TIDieR) guidelines is summarised in
Table 2
^
70
^.

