**physiotherapist training workshop** will be delivered by two members of the research team ([name] and [name]). This two-hour session will include review of knee joint assessment, exploring individual patient beliefs and expectations about their knee pain, delivering tailored patient education, exercise prescription, self-management skills and techniques to maximise patient adherence to a management plan. The workshop will focus on training physiotherapist to adopt a collaborative approach during the ‘best practice’ session that focuses on listening to the patient, understanding their individual concerns and worries, delivering information to reduce fear and address misconceptions, before designing a plan focused on their own goals and interests and delivering tailored education and an exercise programme. This session will be accompanied by a training manual to ensure standardisation of training and material delivered. While training content for clinicians is standardised, physiotherapists will be encouraged to individualise the patient sessions. In addition to the training workshop, physiotherapists will listen to a thirty-minute pre-recorded webinar on addressing common patient misconceptions and beliefs about knee pain. The training manual will include written guidance on the core components of the ‘best practice’ session and additional educational resources on knee pain and communication tips.

**
*Patient intervention.*
** The patient intervention consists of an ‘enhanced consultation’ with their GP and a ‘best practice’ physiotherapy session delivered within two weeks of their GP visit. The patient intervention will be guided by clinical guidelines and include education, exercise and where appropriate, weight management advice
^
26
^. A core focus will be boosting self-management skills and empowering patients with information and resources to manage their symptoms, without the need for inappropriate imaging or surgical consultations. These intervention components will be delivered briefly during the GP consultation through verbal and written information, and addressed more comprehensively during the physiotherapy ‘best practice’ session and using printed and video resources.

a)The ‘

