** Data collected on feasibility of recruitment will include the number of eligible GP practices and GPs approached, the number of GPs attending the educational workshop who consented to participate, the number of patients screened by the GP who consented to be contacted by the researcher, the number of patients contacted by the researcher who consented to participating, reasons for declining to participate or ineligibility (logged by either participating GP or researcher responsible for enrolling patients) and the number of recruited participants who attended the ‘best practice’ physiotherapy intervention. The retention rate is the proportion (%) of enrolled patients who complete the 12-week (primary endpoint) and 6-month follow-up. Retention rate for GPs will be the proportion who engaged with the study by referring at least one patient to the ‘best practice’ physiotherapy session by the end of the recruitment period. The follow-up response rate is the proportion (%) of returned outcome forms at 12-weeks and 6-month follow-up and the proportion (%) of missing data. Data will be collected on adherence to study procedures around the referral to physiotherapy and completeness of referral forms and other study documentation by GPs and physiotherapists adherence to protocols around these.

Qualitative data from individual GP interviews will enhance quantitative data collection, and explore barriers and facilitators to recruitment. It will also explore the ease of procedures like explaining the study to patients and referring to the physiotherapy session. Patients will be asked about what motivated them to take-part in the study. Interviews with both HCPs and patients will seek to understand the burden associated with any outcomes measures.

**
*Intervention acceptability.*
** Acceptability is the perception among stakeholders that a given treatment, service, practice, or innovation is agreeable, palatable, or satisfactory
^
71
^. Acceptability should be assessed based on the participants’ direct experience or knowledge of various dimensions of the intervention delivered.

Intervention acceptability will be measured quantitively with HCPs and patients using the Theoretical Framework of Acceptability-Based Questionnaire (TFA-BQ). The validated generic TFA-BQ was developed as an adaptable tool to measure acceptability across various healthcare interventions
^
74

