** The EuroQol Five-Dimensional Questionnaire (EQ-5D-5L) measures across five dimensions (mobility, self-care, usual activities, pain/ discomfort and anxiety/depression). The response options range from no problems (1) to unable or extreme problems (5). Overall health status is rated on a visual analogue scale from 0 (worst imaginable health) to 100 (best imaginable health)
^
85
^. Validity and reliability has been demonstrated in people with knee osteoarthritis populations
^
86
^.

**
*Global rating of change.*
** Self-rated overall level of improvement in knee symptoms (pain and physical function) will be assessed. Participants will be asked to respond to the questions: ‘Overall, how has your knee pain changed since the start of the study?’ and ‘Overall, how has your knee function changed since the start of the study?’ using Likert scale (7-point) ranging from ‘much worse’ to ‘much better’.

**
*Satisfaction with care.*
** Participants will be asked to rate the “overall satisfaction with the care you received in this study” using a 7-point scale ranging from “extremely unsatisfied” to “extremely satisfied”

**
*Adherence to the exercise and physical activity plan.*
** Adherence to the exercise and physical activity plan agreed with the physiotherapists will be rated by the patient participant on an 11-point Numerical Rating Scale (0 = not at all and 10 = completely as instructed).

**
*Recovery expectations.*
** Expectation of recovery are assessed using a 7-point ordinal scale in response to the question “How much do you expect your knee problem to change in the next 6 months?” ranging from ‘completely recovered’ to ‘worse than ever’.

**
*Use of health care and co-interventions for knee pain.*
** A self-report checklist will record visits to health care providers (additional physiotherapy and GP consultations, other health professional or secondary care consultations), injection use, complementary therapies and imaging between baseline to 12 weeks and at 6-month follow-up using a customised questionnaire.

**
*Change in pain medication usage.*
** Self-report change in pain medication use from baseline to 12-week and 24 follow-up will be assessed with a 7-point Likert scale (much less to much more).

**
*Number of working days missed.*
** The number of work days (paid employment or unpaid work) missed due to the knee problem since baseline will be recorded.

**
*Adverse events.*

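### Excluding enrolled patients who have knee surgery during follow-up selects on an outcome-related event: it flatters health-care use and biases KOOS-PS change in an unknown direction

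*Protocol article*

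**What the plan says.** The rule is in the protocol article's section on concomitant care: "Accessing knee surgery (i.e. arthroscopy) during the follow-up period would result in the patient being excluded from the study". The same section allows other, non-surgical treatment and says of it: "Utilisation of these co-interventions will be captured by the health utilisation questionnaire at 12 weeks and 6 months".

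Other parts of the article bear on the rule:

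- **Purpose.** The opening of the intervention section says that consistent early management should have the effect of "thereby reducing unnecessary referral to secondary care and inappropriate imaging". The patient-intervention text wants patients to manage symptoms "without the need for inappropriate imaging or surgical consultations".
- **Further treatment.** The description of the physiotherapy session ends by promising that the follow-up questionnaires will record whatever further treatment a patient receives.
- **Utilisation items.** The checklist covers visits to health-care providers, including secondary care, then "injection use, complementary therapies and imaging between baseline to 12 weeks and at 6-month follow-up using a customised questionnaire". Surgery is not named.
- **Retention.** "The retention rate is the proportion (%) of enrolled patients who complete the 12-week (primary endpoint) and 6-month follow-up".
- **Clinical outcome.** Preliminary efficacy is the change in KOOS-PS. The quantitative analysis section treats change results as descriptive and exploratory, but uses the KOOS-PS means and confidence intervals to inform the sample size of a later RCT. Objective 8 under Aims asks for the magnitude and variability of change.
- **Size.** "The feasibility of the intervention will be explored by recruiting 36 eligible patients, 15 GPs and five physiotherapists", and "a formal sample size calculation has not been carried out".

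**The concern.** Exclusion before enrolment defines the population. Exclusion after enrolment, triggered by something that happens during follow-up, changes who is analysed according to how they fared. Here the trigger is not incidental. A patient who reaches arthroscopy within six months has gone down the route that the pathway is meant to make less necessary, and is among the most informative patients for judging it.

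Three things are at stake. First, health-care use would be described without the patients who probably used the most secondary care and imaging. Secondly, the KOOS-PS figures that feed a later trial would come from a subset selected on a post-enrolment event. Thirdly, a feasibility study rehearses procedures for that trial, and there the same rule would be an exclusion after randomisation.

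**Working it through.** There is no stated sample size calculation, surgery rate or KOOS-PS effect to reproduce. The check sets the rule beside the other sections and then sizes it under stated assumptions.

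**1. Which data are lost**

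Under Table 3 and the adverse-event text, KOOS-PS, health-care use and prompted harms are collected at 12 weeks and 6 months. The acceptability questionnaire and satisfaction with care are collected at 12 weeks only.

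- Surgery before 12 weeks: both later forms are lost.
- Surgery between 12 weeks and 6 months: the 6-month form is lost. The 12-week form should already have been collected, and nothing says that it is discarded.

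In both cases the promise that follow-up questionnaires will record further treatment cannot be met for the patients concerned.

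**2. How many patients**

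N = 36 is from the protocol. The number of operated patients, k, is an assumption.

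- Share affected = k/36: 1/36 = 2.8%, 3/36 = 8.3%, 6/36 = 16.7%.
- Chance that the rule is triggered at least once = 1 − (1 − p)^36, for an assumed surgery probability p: 30% at p = 1%, 67% at 3%, 84% at 5%, 98% at 10%.

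**3. Health-care use**

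Among patients who remain, surgery is zero by construction, whatever k is. The referrals and imaging that led to surgery, where they would have been reported on a later form, disappear as well. This bias favours the intervention.

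**4. KOOS-PS change**

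The protocol scores KOOS-PS from 0 to 100, higher being better. Assume that non-operated patients gain 10 points and operated patients would have changed by d. For this illustration every other form is returned.

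Mean over all patients = [(36 − k) × 10 + k × d] / 36. Error from exclusion = 10 − that mean.

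| k | d = −10 | d = 0 | d = +10 | d = +20 |
|---|---|---|---|---|
| 1 | +0.56 | +0.28 | 0 | −0.28 |
| 3 | +1.67 | +0.83 | 0 | −0.83 |
| 6 | +3.33 | +1.67 | 0 | −1.67 |

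Example for k = 3, d = −10: (33 × 10 − 3 × 10)/36 = 300/36 = 8.33, and 10 − 8.33 = 1.67. For k = 3, d = +20: (330 + 60)/36 = 10.83, and 10 − 10.83 = −0.83. A positive entry means that exclusion overstates improvement. The sign turns on how operated patients would have scored, which the protocol cannot say.

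**5. Retention**

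Compare three treatments of the operated patients, with k = 3. The last column assumes that operated patients would return their forms.

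| Other losses | Excluded, kept in enrolled denominator | Excluded, also removed from denominator | Followed up |
|---|---|---|---|
| 0 | 33/36 = 91.7% | 33/33 = 100% | 36/36 = 100% |
| 4 | 29/36 = 80.6% | 29/33 = 87.9% | 32/36 = 88.9% |

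On the protocol's own denominator the rule lowers retention. The gap between the first two columns is the ambiguity left by calling these patients both enrolled and excluded.

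**The case against.** The strongest reply has four parts.

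**The study is small and exploratory.** It has one arm, 36 patients and no stated hypothesis test, and effectiveness is not its primary aim. The progression criteria are in an extended-data file that is not shown, so no effect on a go/no-go decision can be demonstrated. This stands and limits severity.

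**Surgery may be rare.** The Introduction says that adult orthopaedic waiting lists are the longest in the country, so public surgery soon after a first GP consultation looks unlikely. It also says that 44% of citizens hold private insurance, so earlier access is possible. No rate is given, so only a range can be offered.

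**Post-surgery scores mix in another treatment.** Whether they belong in the main KOOS-PS summary is a legitimate choice of estimand. That is a reason to state how the scores are handled, not a reason to stop collecting them.

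**The event may not be invisible.** The team must learn of surgery to apply the rule, and a CONSORT-style flow diagram could show the exclusions. The customised questionnaire is only summarised in the article. The protocol nevertheless makes no commitment to count surgery.

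A reader might also infer more than the documents support:

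- *That retention is flattered.* This is so only if excluded patients also leave the denominator, which nothing says.
- *That KOOS-PS improvement is inflated.* This needs operated patients to do worse than the others. The Introduction describes gains from exercise as similar in size to those from surgery, which gives no basis for fixing the sign.
- *That acceptability and satisfaction describe only patients who avoided surgery.* These are lost only for surgery before 12 weeks, and patient interviews are planned within about a month of physiotherapy where possible.
- *That harms are lost entirely.* Events reported by patients, GPs or physiotherapists also go into a log. Only the questionnaire prompts are lost.
- *That a surgery rate of 0% will be reported, or that pre-surgery data will be discarded.* The article says neither.

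**Conclusion.** The point holds, at moderate importance. The protocol fixes a rule that removes enrolled patients because of an event closely related to the intervention's purpose, and the rule does not fit the promise to record all further treatment. The effect on health-care use is favourable to the intervention. The effect on KOOS-PS change has no fixed sign: in the illustration it runs from an overstatement of 3.33 points to an understatement of 1.67 points. The effect on retention, by the protocol's definition, is downward.

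The size depends on the unstated number of surgeries. The range of 1 to 6 in 36, or 2.8% to 16.7%, is an assumption, as are the KOOS-PS changes. Avoiding operations is not itself one of the eight listed objectives. The link to surgery runs through the stated aims on referral and surgical consultation.

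**What to change.** Replace the exclusion sentence with wording such as: *Knee surgery during follow-up does not end study participation or data collection. The patient is still asked to complete the 12-week and 6-month questionnaires and stays in every enrolled-patient denominator.*

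In addition:

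- add knee surgery (type and date) to the utilisation questionnaire and report the count;
- summarise KOOS-PS for all patients with data, regardless of surgery, with a sensitivity summary that omits post-surgery scores;
- if any patient has already been excluded under the rule, report the number and timing and keep that patient in the retention denominator.

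The cost is a short amendment and one added questionnaire item. Recruitment was under way when the article was written, so the change should go through the route that its Trial status section sets for deviations: ethics board, registry and final report. The downside is small: some post-surgery scores enter the main summary, and the sensitivity summary shows their influence. The change concerns only which data are collected and counted, and leaves clinical decisions about surgery untouched.

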### Outcomes

**Feasibility and implementation outcomes**

Data will be collect on implementation and feasibility outcomes to inform decisions about the need for further evaluation of the KNEE-DEeP intervention and a fully-powered trial. Proctor and colleagues framework on outcomes for implementation research was used to select a series of appropriate feasibility and implementation outcomes
^
71
^. Data will be collected on intervention feasibility, intervention acceptability, the feasibility and acceptability of study procedures, intervention fidelity, and preliminary efficacy. Quantitative data using self-report questionnaires and qualitative interview data from both HCPs and patients will be integrated to gain a comprehensive understanding of intervention delivery and implementation processes. Incorporating qualitative data collection is recommended given the capacity to this type of data to add depth to the interpretation of such feasibility study evaluations
^
72
^.
Table 1 illustrates the timing of quantitative and qualitative data collection.
Table 3 summarises all data collection from patient participants.

**Table 3. T3:** Summary of quantitative data collection from patient participants.

Domain	Measurement Tool	Baseline	12 weeks	24 weeks
*Descriptive data*				
Age, gender, self-report weight and height		X		
Education level		X		
Employment status and occupation		X		
Current pain medication use		X		
History of knee injury, kneeling occupation or previous surgery		X		
Symptom duration				
Other knee symptoms		X		
Other pain sites		X		
Comorbidities		X		
*Primary Clinical Outcome Measures*				
Knee function	KOOS-PS	X	X	X
*Secondary Clinical Outcome Measures*				
Knee pain	KOOS pain subscale	X	X	X
Pain self-efficacy	PSEQ-2	X	X	X
Fear avoidance beliefs	FABQ	X	X	X
Health related quality of life	5Q-5D-5L	X	X	X
Satisfaction with care	Self-rated on 7-point ordinal scale for GP and physiotherapy care		X	
Global rating of change	Self-rated on 7-point ordinal scale		X	X
Number of working days missed	Self-reported			
*Additional Measure*s				
Recovery Expectations	5-point ordinal scale	X		
Adherence to the exercise and physical activity plan	Self-rated on 11-point NRS		X	
Data on healthcare utilisation	Self-reported use of health services and co-interventions		X	X
Change in pain medication use	Self-rated on 7-point Likert scale		X	X
Intervention acceptability	TFA Questionnaire		X	
Harms	Self-report of adverse events		X	X

EQ-5D-5L, EuroQol-5 Dimensions-5 Levels; FABQ, Fear Avoidance Beliefs Questionnaire; KOOS, Knee Injury and Osteoarthritis Outcome Score; KOOS-PS, Knee Injury and Osteoarthritis Outcome Score Physical Function Short Form; NRS, Numerical Rating Scale; PSEQ-2, Pain Self-Efficacy Scale Questionnaire 2 item short form; TFA, Theoretical Framework of Acceptability.

**
*KNEE-DEeP intervention feasibility.*
** Feasibility is the extent to which a new treatment or an innovation can be successfully used or carried out in a given setting
^
71
^. A feasibility questionnaire containing a previously validated measure to assess intervention feasibility will be completed by participating physiotherapists and GPs
^
73
^. The Feasibility of Intervention Measure (FIM) is a 4-item scale that measures the extent to which a new intervention can be successfully delivered within a given setting. Items are measured on a 5-point Likert scale (Completely Disagree-Completely Agree) and a mean score is calculated.

Qualitative one-to one interviews with HCPs will explore aspects of feasibility, including if the GP ‘enhanced consultation’ and ‘best practice’ physiotherapy session were practical and feasible for the respective HCPs to deliver. HCPs perspectives on how, why and for whom the interventions did or did not work, and possible barriers to future delivery of the intervention within the broader health care system will also be explored through these interviews. Patients will be interviewed to understand their perceptions of the relevance, usefulness and feasibility of the intervention. Whether participants felt their confidence and ability to manage their knee pain had changed in response to the intervention will also be explored.

**
*Feasibility and acceptability of KNEE-DEeP study procedures.*
** Data collected on feasibility of recruitment will include the number of eligible GP practices and GPs approached, the number of GPs attending the educational workshop who consented to participate, the number of patients screened by the GP who consented to be contacted by the researcher, the number of patients contacted by the researcher who consented to participating, reasons for declining to participate or ineligibility (logged by either participating GP or researcher responsible for enrolling patients) and the number of recruited participants who attended the ‘best practice’ physiotherapy intervention. The retention rate is the proportion (%) of enrolled patients who complete the 12-week (primary endpoint) and 6-month follow-up. Retention rate for GPs will be the proportion who engaged with the study by referring at least one patient to the ‘best practice’ physiotherapy session by the end of the recruitment period. The follow-up response rate is the proportion (%) of returned outcome forms at 12-weeks and 6-month follow-up and the proportion (%) of missing data. Data will be collected on adherence to study procedures around the referral to physiotherapy and completeness of referral forms and other study documentation by GPs and physiotherapists adherence to protocols around these.

Qualitative data from individual GP interviews will enhance quantitative data collection, and explore barriers and facilitators to recruitment. It will also explore the ease of procedures like explaining the study to patients and referring to the physiotherapy session. Patients will be asked about what motivated them to take-part in the study. Interviews with both HCPs and patients will seek to understand the burden associated with any outcomes measures.

**
*Intervention acceptability.*
** Acceptability is the perception among stakeholders that a given treatment, service, practice, or innovation is agreeable, palatable, or satisfactory
^
71
^. Acceptability should be assessed based on the participants’ direct experience or knowledge of various dimensions of the intervention delivered.

Intervention acceptability will be measured quantitively with HCPs and patients using the Theoretical Framework of Acceptability-Based Questionnaire (TFA-BQ). The validated generic TFA-BQ was developed as an adaptable tool to measure acceptability across various healthcare interventions
^
74
^. Questions on the seven component constructs (affective attitude, burden, ethicality, intervention coherence, opportunity costs, perceived effectiveness and self-efficacy) are adapted for the KNEE-DEeP study and each rated using a five-point Likert scale ranging from ‘Strongly disagree’ to ‘Strongly agree’.

Qualitative data collection with HCPs will explore the acceptability of the HCP intervention and their experience of the training workshops. How acceptable the HCPs perceived the patient intervention to be will also be discussed during these interviews. Patient interviews to explore acceptability will focus on understanding if patients liked and valued the various components of the KNEE-DEeP intervention as it was delivered.

**
*KNEE-DEeP fidelity.*
** Fidelity is the degree to which an intervention was implemented as the developers of the intervention intended
^
71,
75
^. Fidelity of delivery and receipt of the KNEE-DEeP intervention will be assessed using quantitative and qualitative data collection. While it is not practical to measure directly GPs delivery of the components of the ‘enhanced consultation’, an indirect or proxy measure will be used in the form of two checklists. GPs will indicate their delivery of the four components of the ‘enhanced consultation’ on a checklist as part of completing the ‘best practice’ physiotherapy referral form. Patient participants will complete a checklist as part of their baseline questionnaire, indicating receipt of these intervention components during the GP consultation. At the end of each session, physiotherapists delivering the KNEE-DEeP ‘best practice’ session will complete treatment logs. This consists of a checklist documenting the key session components (e.g., clinical assessment, exploring beliefs, aspects of patient education, self-management skills, goal setting etc).

Qualitative data on aspects of fidelity, including delivery and receipt of HCP training, delivery of the patient intervention by HCPs and enactment of the clinical intervention by patients, will be gathered during interviews with a subset of patients and HCPs.

**
*Preliminary efficacy.*
** Preliminary efficacy will be assessed by the change in the primary clinical outcome measure of self-reported knee-function. All primary and secondary clinical outcome measures are described below.

